#### Staff support system

The staff support system is an integral component of the PCCI. Following the workshop, the PI and the SLP trained the facility SLP on how to support staff to use the communication care plan in everyday practice. Supporting the staff at the bedside is a credible model that has been widely used in education research [40-42], and it is highlighted in the knowledge translation literature as useful in enhancing skill development and change [43,44]. In this study, supporting nursing staff involves providing positive feedback to nursing staff who acquire new skills, observing nursing staff interact with their patients, and providing teaching at the bedside when necessary. The facility SLP is asked to support each nursing participant for 1 hour a week for a three-week period after the workshop and to provide ongoing support. The SLP is available to consult with the facility SLP or educator as required.

### Data collection

The research assistant (RA) was trained in data collection procedures by the PI and SLP on general aging topics, stroke, communication impairments, and confidentiality/privacy issues. The SLP taught and demonstrated the procedures for obtaining self-report data and consent from patients with communication impairments. In addition, the training involved inter-reliability checks on the data collected. The RA is responsible for recruitment, data collection, and data management for the site.

#### Outcome measures

In order to maximize the likelihood of observing a significant effect of the PCCI, we selected outcome measures that demonstrated sensitivity to the intervention in our pilot work. The outcome measures for patient and the nursing staff are described.

#### Patient measures

##### Patient characteristics

We record age, sex, length of stay, education, date of stroke, and co-morbidities (the number of medical diagnoses other than stroke) from the patients’ medical records. The severity of patients’ communication disability as assessed by the Western Aphasia Battery (WAB) is considered as a co-variate; this patient characteristic has been found to influence staff-patient interactions [45].

##### Patient assessments of language and cognition

Language impairments (WAB), visuo-spatial impairment (Birmingham Object Recognition Battery, BORB), visual neglect (Bell’s test), and cognitive impairment (Mini-Mental State Examination, MMSE) are assessed. These data are used to determine the patient’s abilities and to determine the strategies the SLP recommends in the communication care plan.

1. The Western Aphasia Battery (WAB) is a comprehensive, multifactorial battery designed to evaluate a broad range of language impairments that often arise as a consequence of acquired brain dysfunction such as stroke.

2. Birmingham Object Recognition Battery (BORB) – Minimal Feature View Task provides a set of standardized procedures for assessing neuropsychological disorders of visual object recognition, based on tests developed from the cognitive neuropsychological literature. The Minimal Feature View Task assesses low-level aspects of visual perception (using same-different matching of basic perceptual features, such as orientation, length, position and object size and intermediate visual processes, e.g., matching objects different in viewpoint). The BORB has documented validity and reliability and provides normative data that are available for comparison [46].

3. The Bell’s Test is a cancellation test that permits a quantitative and qualitative evaluation of visual neglect which is important when staff attempt to communicate with the patient. It also provides valuable information on how the task is performed and the visual scanning pattern used by the participant. The Bell’s Test is sensitive for detection of mild and moderate neglect and permits a better exploration of the clinical manifestations of attention deficits in space [9].

4. The Mini-Mental State Examination (MMSE) is a widely used brief quantitative measure of cognitive status in adults. It has demonstrated validity and reliability in a variety of populations [47].

#### Patient outcome measures

The patient outcome measures below are collected by the RA. The *primary outcome* is the communication domain of the Stroke and Aphasia Quality of Life (SAQOL).

1. Patients’ quality of life is assessed with the SAQOL. The psychosocial domain, which includes 11-items (alpha of .67) and the communication domain with 7 items (alpha of .73) were selected as they are most responsive to the intervention. The communication domain has demonstrated convergent validity with the American Speech and Hearing Association Functional Assessment of Communication Skills for Adults (r = .55). The psychosocial domain demonstrated convergent validity with the General Health Questionnaire (r = .65) [48].

2. Patients’ satisfaction with care is measured with the Relational Care Scale (RCS)[49], which has acceptable internal consistency (Cronbach’s alpha = 0.87) and test-retest reliability (r = 0.70). The 6-item scale demonstrated sensitivity to change in two studies of patients with communication impairments [26,45].

3. Depressive symptoms are assessed with the 5-item Geriatric Depression Scale[50]. This is a well established measure that has been validated and used to assess depression in adults with aphasia following a stroke [51].

4. Agitation is assessed during nursing staff-patient interactions using the observational measure Pittsburgh Agitation Scale (PAS). The PAS rates the severity of agitation on a scale ranging from 0 to 4 in four general behaviour groups: aberrant vocalization, motor agitation, aggressiveness, and resisting care [52]. Reliability and validity testing of the PAS have been conducted in both acute geropsychiatric units (intraclass correlation coefficient [ICC] of .82) and nursing homes (ICC=.93) [52].

#### Nursing staff measures

##### Nursing staff characteristics

The following data are obtained from the nursing staff by the RA following a nurse-patient observation. Characteristics include age, sex, education level, job status, job category, and length of time employed on the unit. The job category of the staff will be used as a co-variate when analyzing staff outcomes, as staff’s knowledge of communicating with patients with communication impairments differs depending on job category [45]. Most staff members are willing to participate because of the endorsement of our research by administrators at the institution and based on previous recruitment rates for evaluation studies [26,45]. A sample size of 19 staff was sufficient to demonstrate changes in staff’s attitudes in the pilot study.

##### Nursing staff’s evaluation of the nurse-patient communication patterns

For the purpose of developing the individualized communication plans, each staff member is asked to complete the (MECQ-LTC) for the assigned patient. The MECQ-LTC is designed to (i) evaluate the frequency of use of various means of communication employed by the patient and his/her nurse; (ii) evaluate the number of different communication acts realized by the patient; (iii) determine the degree of effort required by nursing staff for efficient communication with a patient in diverse communication situations; and (iv) identify problematic communication situations [24]. The scale has established interrater-reliability and construct validity [24].

#### Nursing staff outcomes

1. Attitudes of the nursing staff toward communicating with patients with communication impairment are measured with the Communication-Impairment Questionnaire (CIQ), an 8-item self-report scale [24]. The measure focuses on the extent to which a staff member espouses a person-centred approach in relating to individuals with communication impairments. Reliability data from the pilot study indicated a Cronbach’s alpha coefficient of .73. In addition, the scale was sensitive to change following communication interventions [24,26].

2. Knowledge of staff working with patients with communication disabilities is measured using the Providers Interactional Comfort Survey (PICS)[20]. The scale has an acceptable reliability with a Cronbach’s alpha coefficient of .81 and has shown sensitivity to a communication intervention [45]. The measure focuses on nurses’ perception of their competence, confidence, willingness, frequency, and scope of practice related to interacting with patients.

#### Assessment of treatment fidelity

To assess for treatment fidelity it is necessary to ensure that procedures are in place to monitor for protocol adherence [53]. We monitor treatment fidelity by assessing staff’s adherence to the strategies outlined in the patient’s communication care plan. The strategies used during nurse-patient interactions are assessed by the Interaction Rating Form (IRF)[54], refined during our pilot work. The IRF includes operationalized observational ratings of strategies that are commonly suggested by SLPs when treating patients with communication impairments [26,54]. For example, items include: did the nurse use open ended questions or pictures, stand on the right side of the patient when communicating, and use gestures during the interactions. High scores indicate high levels of adherence to the treatment. Inter-rater reliability (r=.91-.95) and construct validity (r =.84 to .96 with clinical judgment) have been reported for the IRF [54].

### Statistical analysis

#### Sample size

The primary outcome for the patients is an improvement in the communication domain of the SAQOL (SAQOL-com) from pre- to post-test at 1 month. In our pilot study, the mean SAQOL-com score increased 3.8 units to 21.0 from a baseline score of 17.2 [26]. The baseline standard deviation was 5.0. This provides a Cohen’s standardized effect size of 0.76. A sample size of 44 is estimated to have 90% power to detect this effect using a repeated measures hierarchical regression analysis with an intra-class correlation of 0.40 among the three repeated measures and for an alpha of 0.05 [55].

The primary outcome for the staff is an improvement in the score from pre- to post-test in attitudes related to communicating with patients who have communication impairments (CIQ). In the pilot study, the improvement was 2.4 with a standard deviation of 4.1 providing a Cohen’s standardized effect size of 0.58. A sample size of 55 is estimated to have 80% power to detect this effect using a repeated measures hierarchical regression analysis with an intra-class correlation of 0.40 among the three repeated measures for an alpha of 0.05 [55]. We plan to recruit 60 patients: 30 in the control group and 30 in the intervention group. Each patient assessment will include a nurse-patient interaction; therefore, the subjects will be recruited as nurse-patient dyads.

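### The stated 44 patients for 90% power does not match the 1-month between-cohort endpoint: as a total, 44 gives about 63% (change score) or 78.5% (baseline-adjusted)

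*Protocol article*

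**What the plan says.** All the planning figures are in the patient paragraph of the Sample size section.

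- Endpoint: "The primary outcome for the patients is an improvement in the communication domain of the SAQOL (SAQOL-com) from pre- to post-test at 1 month".
- Effect: "In our pilot study, the mean SAQOL-com score increased 3.8 units to 21.0 from a baseline score of 17.2".
- Spread and standardised effect: "The baseline standard deviation was 5.0", then "This provides a Cohen’s standardized effect size of 0.76".
- Result: "A sample size of 44 is estimated to have 90% power to detect this effect using a repeated measures hierarchical regression analysis". The further inputs given for it are a correlation of 0.40 between the three occasions and a 5% significance level.

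The section then plans 60 patients, 30 in each group. The opening of Methods/design describes a non-equivalent control group design. It lists the three measurement occasions as a baseline before the intervention, a post-test within 4 weeks of its completion and a post-test at 3 months. The Background describes the pilot as training for 18 nurses on one unit and mentions no control group.

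**The concern.** The endpoint is a change over one interval, baseline to 1 month, compared between two cohorts. The variance assumption refers to three repeated measures, one of them taken before any intervention effect can exist. A calculation that lets all three carry the full effect gains precision that the 1-month comparison does not have.

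The effect size raises a second question. A gain from 17.2 to 21.0 within a trained pilot group equals a between-cohort difference only if controls gain nothing over the same interval.

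What is at stake is how the result is read. With 44 said to suffice for 90%, a planned 60 appears to leave 16 patients in hand. If that margin is not there, a null result could be taken as coming from a trial with more than 90% power when it had less.

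**Working it through.** **Inputs (Sample size section).** Difference 3.8 = 21.0 − 17.2; SD 5.0; d = 3.8/5.0 = 0.76; correlation ρ = 0.40; alpha 0.05; power 90%. Sidedness is not stated; two-sided is assumed because it reproduces the printed figure. Normal approximation throughout.

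**Formulas.** With variance factor f (variance of the analysed quantity divided by SD²):

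- n per group = 2 (1.96 + 1.2816)² f / d²
- power = Φ( d √(n / 2f) − 1.96 )

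**Reproducing 44**

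1. *As a total: two groups compared on the mean of three measures.* f = (1 + 2 × 0.40)/3 = 0.60. n = 2 × 10.508 × 0.60 / 0.5776 = 21.83 per group, total 43.66, hence 44.
2. *As a per-group number: difference in change between two occasions.* f = 2(1 − 0.40) = 1.20. n = 2 × 10.508 × 1.20 / 0.5776 = 43.66 per group, hence 44 per group and 88 in total.

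The staff figure of 55 (2.4/4.1, 80% power) does not separate the two readings. The first gives a total of 54.97 and the second gives 54.97 per group. A one-group before-after calculation also gives 21.83, or 44 if 22 is doubled; for staff it gives 27.49, or 56 if 28 is doubled.

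**What the first reading assumes.** It needs a 0.76 SD difference at baseline as well as at both follow-ups. With no difference at baseline and 0.76 SD at both follow-ups, the three-measure mean differs by (2/3) × 0.76 = 0.507 SD, and power at 44 for that mean is 58%.

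**Power for the stated 1-month between-cohort endpoint, d = 0.76**

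| Analysis at 1 month | f | Power, 44 total | Power, 60 total | Total for 90% |
|---|---|---|---|---|
| Difference in change | 1.20 | 63% | 77% | 88 |
| 1-month score alone | 1.00 | 71% | 84% | 74 |
| Baseline-adjusted, f = 1 − ρ² | 0.84 | 78.5% | 89.5% | 62 |

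Example, difference in change with 22 per group: 0.76 × √(22/2.4) − 1.96 = 0.34, and Φ(0.34) is about 0.63.

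Using the t distribution lowers these slightly: 61% and 77% at 44, and 75% and 88.5% at 60, for change and baseline-adjusted respectively. A one-sided test does not rescue 44 either: 74% (change), 81% (1-month score) and 87% (baseline-adjusted).

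**Sensitivity to control-group change (assumption; the article gives no figure).** If controls gain 1 point, d = (3.8 − 1)/5.0 = 0.56. Power at 60 is then 51% for a difference in change and 66% baseline-adjusted; at 44 it is 40% and 53%.

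**The case against.** **The method is not stated.** The article names a repeated measures hierarchical regression and cites a source that is not available here. A reader might infer that the authors averaged three measures including baseline. The documents do not establish this, since 44 and 55 come out equally well as per-group numbers for a difference in change. This objection stands, so the point is confined to the mismatch, which holds under either reading.

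**The trial recruits 60, not 44.** A reader might infer that the trial as planned is badly underpowered. With baseline adjustment, 60 evaluable patients give about 89.5%, close to the stated target if controls do not change. Objective #1 plans a hierarchical model with covariates and does not commit to a raw change score. This stands as well: the size of the shortfall at 60 depends on the analysis.

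**The longitudinal model may be stronger.** Objective #1 expects the effect to be maintained after the first post-test. A baseline-adjusted mean of the two follow-ups has f = (1 + 0.40)/2 − 0.16 = 0.54 and gives 93% at 44. That is correct, but it tests a different quantity from "an improvement in the communication domain of the SAQOL (SAQOL-com) from pre- to post-test at 1 month", so it does not support the sentence as written.

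**Pilot gains are commonly used for planning.** This is true, and no control-group gain is documented. The sensitivity figures show dependence on an assumption; they do not demonstrate a loss of power.

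**Conclusion.** The 44/90% statement is wrong for the endpoint it is attached to. As a total, 44 gives about 63% power at 1 month for a difference in change, or 78.5% with baseline adjustment. As a per-group number it contradicts the planned 30 per group. The planned 60 gives about 77% or 89.5%. The apparent 16-patient margin is therefore gone: 90% needs 62 in total with baseline adjustment and 88 for a difference in change.

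These figures rest on d = 0.76, ρ = 0.40, a two-sided 5% test, all patients evaluable at 1 month, no control-group change and no allowance for the crossed staff effect in Objective #1. Evaluability is not assured: Methods/design ties control follow-up to discharge, and Setting and sample describes one unit with stays of up to 1 month.

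Two stronger conclusions are not supported. The first is that baseline adjustment is the required analysis: with non-equivalent groups, adjusted and change-score comparisons can answer different questions, and the choice belongs to the trial team. The second is that controls will improve by a particular amount. The document only leaves unsaid that using the pilot gain as the between-cohort difference assumes they will not.

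**What to change.** In the Sample size section, delete the statement that 44 patients give 90% power. In its place:

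- Name the 1-month between-cohort contrast that the trial will use.
- State its power with 60 evaluable patients (30 per cohort), for a 3.8-point difference, SD 5.0 and correlation 0.40: about 77% for a difference in change, or about 89% if baseline-adjusted.
- Say that this treats the pilot before-after gain as the between-cohort difference, and so assumes no change in controls.
- Add one sensitivity line, labelled as an assumption. For example, a control gain of 1 point would give about 51% (change) or 66% (baseline-adjusted).

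The cost is rewording and a less favourable stated power. No extra patients are needed. According to Trial status, the intervention cohort was still accruing, with 16 enrolled, so the contrast could still be named before that cohort was complete.

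### The staff figure of 55 for 80% power comes from a formula averaging three occasions, which fits neither the pre-to-post CIQ endpoint nor the staff schedule of baseline and one post-test

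*Protocol article*

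**What the plan says.** The Sample size section defines the staff endpoint as a change: "The primary outcome for the staff is an improvement in the score from pre- to post-test in attitudes". The pilot input follows: "In the pilot study, the improvement was 2.4 with a standard deviation of 4.1 providing a Cohen’s standardized effect size of 0.58". From this the article concludes: "A sample size of 55 is estimated to have 80% power to detect this effect using a repeated measures hierarchical regression analysis". The correlation assumed for that figure is 0.40 over three measures, at alpha 0.05.

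The patient paragraph of the same section labels its SD differently: "The baseline standard deviation was 5.0". Patients are sized at 44 for 90% power with an effect size of 0.76 and the same correlation and number of measures.

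The sections disagree on when staff are measured:
- Methods/design: baseline, then post-test 2 or before the patient's discharge, so one follow-up.
- Specific aims: staff effects at 1 and 3 months, so two follow-ups.
- Sample size: three repeated measures.
- Objective #2: the same hierarchical approach as for patients, at each time point.

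**The concern.** Averaging a nurse's score over three occasions is a different contrast from the gain between two occasions, and the two have different variances. The factor used for the average cannot be carried over to the gain. The input is also unclear. The factor needs a single-score SD, yet the text ties 4.1 to the improvement without saying whether it is the SD of the change or of a score.

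At stake is the power claimed for a declared primary outcome. If the true figure is nearer 50–75% than 80%, a null CIQ result would be over-read as evidence against an effect that the trial was said to be well placed to detect.

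**Working it through.** **Inputs.** From Sample size: gain δ = 2.4, SD 4.1, correlation ρ = 0.40, three measures, alpha 0.05, N = 55, power 80%. From Methods/design: one staff follow-up. Assumed, because not stated for staff: two equal groups, two-sided alpha, and 55 as a total.

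**Formulas.** For single-score SD s and variance factor f:
- N = 4 · f · (1.960 + z_power)² · (s/δ)²
- power at N = Φ( δ√N / (2s√f) − 1.960 )

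**Reproducing the plan.** The average of three occasions has f = (1 + 2 × 0.40)/3 = 0.60.
- Staff, 80%: 4 × 0.60 × 7.849 × (4.1/2.4)² = 54.97, so 55. Power at 55 is 80.0%.
- Patients, 90%: 4 × 0.60 × 10.507 / 0.76² = 43.66, so 44.

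Both printed figures come out. A one-sided test gives 43.3 for staff and a one-group paired test gives 22.9, so neither is the source of 55.

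**The contrast that the endpoint describes.** If 4.1 is the SD of change, ρ = 0.40 implies s = 4.1/√(2 × 0.60) = 3.74. If 4.1 is a single-score SD, s = 4.1 and the SD of change is 4.1 × √1.2 = 4.49.

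| Contrast | f at ρ = 0.40 | Power at 55 if 4.1 is SD of change (N for 80%) | Power at 55 if 4.1 is single-score SD (N for 80%) |
|---|---|---|---|
| Change to one post-test | 2(1 − 0.40) = 1.20 | 58% (91.6) | 51% (109.9) |
| One post-test, baseline-adjusted | 1 − 0.40² = 0.84 | 74% (64.1) | 66% (77.0) |
| Change to mean of two post-tests | 0.70 + 1 − 0.80 = 0.90 | 71% (68.7) | 63% (82.5) |
| Mean of two post-tests, baseline-adjusted | 0.70 − 0.16 = 0.54 | 90% (41.2) | 84% (49.5) |
| Plan's average of three occasions | 0.60 | 87% (45.8) | 80% (55.0) |

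The first two rows match the schedule in Methods/design. With the t distribution, 58% becomes 57%.

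**Sensitivity to ρ.** The 58% does not depend on ρ. With 4.1 as the SD of change, the baseline-adjusted 74% would be 80% at ρ = 0.2, 77% at 0.3, 71% at 0.5 and 68% at 0.6.

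**What the last row assumes.** Averaging over all three occasions yields 2.4 only if the groups already differ by 2.4 at baseline. With no baseline difference and 2.4 at two post-tests, the average difference is 2 × 2.4/3 = 1.6. Power at 55 is then about 53% (s = 3.74) or 46% (s = 4.1).

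**The case against.** A reader might infer that the whole problem is an SD of change put into a single-score formula. The arithmetic does not support that. Converting 4.1 to 3.74 and leaving everything else alone raises power at 55 to 87%, so at ρ = 0.40 the label alone makes the plan's figure conservative. The shortfall arises from the contrast and the occasions. The 87% itself rests on a full group difference at baseline, so it does not rescue the 80% for a pre-to-post endpoint.

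A reader might also infer that 55 cannot give 80% on any reading. That is too strong. Specific aims implies two staff follow-ups, and two post-tests with baseline adjustment give 84–90%. The document does not settle which schedule applies.

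Three further objections deserve an answer:
- **No untrained staff group is clearly described.** A one-group pre-post test with 4.1 as the SD of change would have 99% power at 55. But the printed 55 does not come from such a test, and Objective #2 carries over the approach used for the two-group patient comparison.
- **55 might be per group.** Because (1 + 2ρ)/3 equals 1 − ρ at ρ = 0.40, 55 per group also fits a change-score calculation with 4.1 as a single-score SD. However, the patient figure of 44 is met by the planned 60 only as a total, and the staff figure is presented in the same way.
- **Power at 55 is hypothetical when 30 staff are planned.** True, but the recruitment number is a separate matter; the calculation would need correcting even with 55 nurses.

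Finally, only the pilot data can show which SD 4.1 is. The article does not say, so this point does not assert either.

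**Conclusion.** The concern holds in limited form. The statement "A sample size of 55 is estimated to have 80% power to detect this effect" rests on a variance factor for a three-occasion average, whereas the endpoint is a pre-to-post gain and Methods/design gives staff one post-test. On that endpoint and schedule, 55 in total gives about 51–58% unadjusted or 66–74% baseline-adjusted, that is 6 to 29 points below the stated figure.

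These figures rest on two equal groups, two-sided alpha 0.05, 55 as a total and ρ = 0.40 (the 58% does not need ρ). They do not show that 80% is out of reach under every design, nor that the SD label alone is at fault.

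**What to change.** In the staff paragraph of Sample size:
1. State whether 4.1 is the SD of the CIQ change or of a single CIQ score, from the pilot data.
2. Reconcile the number of staff measurement occasions across Specific aims, Methods/design and Sample size.
3. Replace the 0.60 factor with the variance for the intended contrast, and say that 55 is a total over two groups, if that is so.
4. Restate the power. Under the Methods/design schedule this is about 58% (SD of change) or 51% (single-score SD) for the difference in improvement, and about 74% or 66% with baseline adjustment. If two staff post-tests are in fact taken, give the figure for that design.

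Under Objective #2, analyse post-test CIQ with baseline CIQ as a covariate. Baseline CIQ is already collected, and at ρ = 0.40 adjustment adds about 15 points of power over the change score.

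The cost is a revised paragraph, one model covariate and a less favourable stated power. No added enrolment or data collection is asked for.

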**Methods/design:**

A quasi-experimental repeated measures non-equivalent control group design in a complex continuing care facility is being used. Patients with a communication impairment post-stroke admitted to the facility are eligible to participate. All staff nurses are eligible. Baseline data are collected from staff and patients. Follow-up will occur at 1 and 3 months post-intervention. Subject recruitment and data collection from 60 patients and 30 staff will take approximately 36 months. The Patient-Centred Communication Intervention consists of three components: (1) development of an individualized patient communication care plan; (2) a one-day workshop focused on communication and behavioural management strategies for nursing staff; and (3) a staff support system. The intervention takes comprehensive patient assessments into account to inform the development of communication and behavioural strategies specifically tailored to each patient.

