## Methods/design

A quasi-experimental repeated measures non-equivalent control group design guides this study. In this design, control subjects from two units in one facility were enrolled and followed for up to three months, dependent on when they were discharged. Once the control subjects were accrued, staff from the facility were trained in the PCCI model. Currently the intervention cohort is being enrolled and followed.

Outcome data pertaining to the variables of interest are obtained from the patient participants in the control and experimental units at 3 different time points: 1) baseline, prior to delivering the intervention; 2) post-test 1, within 4 weeks after completion of the intervention; and 3) post-test 2, 3-months after completion of the intervention. Outcome data pertaining to the nursing staff are obtained at baseline and again at post-test 2 or prior to the patient’s discharge. Ethics approval was received from the Toronto Rehabilitation Institute Research Ethics Board #09-009 and from the research facility ethics board #2010-002-1002.

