### Trial status

The trial is now accruing during the intervention phase of the study. Progress to date includes the collection of data on all 30 control subjects; 16 intervention participants are enrolled with an end date of March 2013. Twenty-five staff nurses have agreed to participate in the study and have completed questionnaires.

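### The staff calculation calls for 55 independent units for 80% power, but the plan recruits 30 nurses, so the stated power does not follow from the planned staff number

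*Protocol article*

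**What the plan says.** The Sample size section gives the staff a primary outcome of their own: "The primary outcome for the staff is an improvement in the score from pre- to post-test in attitudes", measured with the CIQ. From the pilot, "the improvement was 2.4 with a standard deviation of 4.1 providing a Cohen’s standardized effect size of 0.58". It then states: "A sample size of 55 is estimated to have 80% power to detect this effect using a repeated measures hierarchical regression analysis". The other inputs named there are a correlation of 0.40, three measures per unit and a 5% significance level. Straight afterwards comes the patient target, "We plan to recruit 60 patients: 30 in the control group and 30 in the intervention group", with a remark that recruitment is by nurse-patient pair. The section sets no staff target.

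That target is in the abstract: "Subject recruitment and data collection from 60 patients and 30 staff will take approximately 36 months". Trial status adds: "Twenty-five staff nurses have agreed to participate in the study and have completed questionnaires". Accrual was still open at that point.

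Three other places bear on the unit and the number of measures:

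- Nursing staff outcomes describes the CIQ as a self-report scale of the staff member's own attitudes.
- Objective #2 analyses it as repeated measures nested within patients, by the same methods as Objective #1, whose model treats staff as a crossed random effect.
- The opening of Methods/design says "Outcome data pertaining to the nursing staff are obtained at baseline and again at post-test 2" (or before the patient's discharge), which is two occasions. Specific aims sets the staff objective at both 1 and 3 months, and Objective #2 speaks of outcomes at every time point.

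**The concern.** A self-reported attitude belongs to the nurse, so the natural independent unit is the nurse. The calculation asks for 55 units and the plan supplies 30 nurses. The dyads would exceed 55, but with 60 dyads and 25 to 30 nurses each nurse appears on average 60/30 = 2 to 60/25 = 2.4 times, and repeated appearances of one nurse do not carry the information of separate nurses. Nesting the staff outcome within patients points the same way, since it makes the patient, not the nurse, the cluster.

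At stake is how a null CIQ result is read. Someone relying on the stated 80% would take it as fair evidence against an effect on attitudes, although the planned staff number does not give that power on the stated calculation.

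**Working it through.** **Inputs.** From Sample size: improvement 2.4, SD 4.1, correlation 0.40, three measures, alpha 0.05, 80% power. From the abstract: 30 staff, 60 patients. From Trial status: 25 staff. Two-sided testing is my assumption; it is what reproduces the plan's figure.

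**1. Reproduce the 55.** For two equal groups compared on the mean of m measures:

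N = 4 (z_alpha/2 + z_power)² × v / d², with v = (1 + (m − 1) × 0.40)/m

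With m = 3, v = 1.8/3 = 0.60. With d = 2.4/4.1 = 0.585:

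N = 4 × (1.960 + 0.842)² × 0.60 / 0.585² = 54.97, i.e. 55.

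Using the rounded 0.58 gives 56.0. The same formula with d = 0.76 and 90% power gives 43.66, i.e. the plan's 44 for patients. So 55 is a total of independent units across two groups.

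**2. Put the planned nurses into that formula.** Power = Φ(d × √(N / (4v)) − 1.96).

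- 30 nurses: Φ(2.070 − 1.96) = 0.544.
- 25 nurses: Φ(1.889 − 1.96) = 0.472.
- 60 units, all independent: Φ(2.927 − 1.96) = 0.833.

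**3. Allow for dyads sharing a nurse.** Suppose 30 nurses supply two dyads each in the same group. The effective number is 60/(1 + k), where k is the within-nurse correlation. The protocol gives no k, so this is a range of assumptions:

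| k (assumed) | Effective N | Power |
|---|---|---|
| 0.05 | 57.1 | 0.815 |
| 0.10 | 54.5 | 0.797 |
| 0.20 | 50.0 | 0.762 |
| 0.40 | 42.9 | 0.696 |
| 1.00 | 30.0 | 0.544 |

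The 80% survives only if k is below about 60/54.97 − 1 = 0.09.

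**4. Number of measures.** With two staff occasions instead of three, v = 1.4/2 = 0.70. The required total becomes 54.97 × 0.70/0.60 = 64.1. Power is Φ(1.916 − 1.96) = 0.482 for 30 nurses and Φ(1.749 − 1.96) = 0.417 for 25.

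**5. A different analysis: within-nurse pre-post comparison.** Paired t test, two-sided 0.05, noncentrality (d/s) × √n:

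| What 4.1 is | s | 30 nurses | 25 nurses |
|---|---|---|---|
| SD of change | 1 | 0.873 | 0.802 |
| Single-time SD, correlation 0.40 | √(2 × 0.6) = 1.095 | 0.808 | 0.727 |

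The protocol does not say which SD 4.1 is.

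**The case against.** The strongest reply is that the staff outcome is defined as a pre- to post-test improvement, no section allocates nurses to two groups, and a within-nurse analysis of the planned 30 would reach 81% to 87%. On that view nothing is short. This stands as far as it goes, and it is why a reader should not infer that the staff aim is underpowered or close to a coin toss. The 54% and 47% belong to the two-group formula behind the 55, not to every analysis that could be run. It does not rescue the sentence as written, because a paired comparison is not how the 55 was obtained.

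Four further points on that side also stand:

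- A reader might infer that the protocol claims its dyads satisfy the 55. It never says so. That link comes from the order of the sentences and from the nesting within patients.
- A reader might infer that there are no untrained nurses to compare with. Methods/design trains staff only after control accrual, so nurses in control-phase dyads were untrained then. Whether the same nurses serve in both cohorts is not stated. If they do, within-nurse correlation would help a between-cohort comparison.
- Twenty-five is an interim count; the plan is 30.
- The crossed random effect for staff in Objective #1 may carry over to Objective #2. It would then deal with clustering in the analysis, but it would not change the sample-size figure.

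**Conclusion.** The concern holds in a limited form. The arithmetic giving 55 is correct, but the figure counts independent units and the plan supplies 30 nurses. On the stated calculation power is about 54% with 30 nurses and 47% with 25, or about 48% and 42% if staff are measured twice. Counting dyads keeps 80% only if two dyads of the same nurse are almost uncorrelated, which is hard to credit for a self-reported attitude; that correlation is an assumption throughout. The number of staff measurements is itself contradictory: two in Methods/design, three in the calculation, and both follow-up times in Specific aims and Objective #2.

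What the documents do not support is a claim that the staff aim must fail for lack of power. That depends on the comparison made, on what 4.1 is, and on whether nurses cross the two cohorts. The point should be fixed, but it concerns Objective 2 only. The patient calculation (44 needed, 60 planned) is not affected.

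**What to change.** In Sample size, delete or correct the statement that 55 gives 80% power for staff, and:

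1. Make the nurse the independent unit, both in the calculation and in the Objective #2 model, with repeated measures nested within nurse and not within patient.
2. Reconcile the number and timing of staff measurements across Specific aims, Methods/design, Sample size and Objective #2.
3. State whether the same nurses serve in the control and intervention cohorts, and hence which comparison the staff test makes.
4. State whether 4.1 is the SD of change or of a single measurement.
5. Restate power for the 30 planned nurses (or the 25 who have agreed) on that basis. If dyads enter the calculation, give the assumed within-nurse correlation and a range around it.

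The cost is rewording, one recalculation and possibly a less favourable stated power. No extra recruitment is needed.
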